### Safety reporting

All adverse event reported by the subjects or observed by the treating physicians will be recorded. In case of serious adverse events (SAE), the principal investigator will be notified by email or telephone within 24 hours. The principal investigator subsequently reports SAE to the Data Safety Monitoring Board (DSMB). This is an independent committee of trial experts, who will focus on both safety monitoring and analysis of effectiveness on unblinded data. The DSMB will perform ongoing safety surveillances, especially with regard to the occurrence of serious adverse events in terms of SICH and serious systemic bleeding within 48 hours. The DSMB can recommend the Steering Committee of the ARTIS-Trial to terminate the trial when there is clear and substantial evidence of harm. All SAE will be reported to the central METC according to their requirements as well.

### Trial size

Based on our own experience in the stroke unit cohort and the results of the rt-PA thrombolysis trials [1] and the SITS-MOST registry [23] it is expected that 50% of the patients with an ischemic stroke treated with rt-PA thrombolysis will have a poor outcome (mRS 3-6). We aim to reduce this percentage by 10%, a relative risk reduction of 20%.

A two group X^2 ^test with a 0,05 two-sided significance level will have 80% power to detect the difference between the control group proportion of 0,50 and an experimental group proportion of 0,40 (odds ratio of 0,667) when the sample size in each group is 400 (total trial size 800). With this sample size, a two-sided 95% confidence interval for the difference between the proportions will extend 0,069 from the observed difference in proportions. With this sample size we are also able to statistically detect a minimal effect size (difference between mean scores of both treatment arms divided by the SD of the control group ) of *d *= 0,20 as benchmark for assessing the relative magnitude of score differences on the continuous AMC Linear Disability Scale (ALDS) which is a secondary outcome parameter.

### Statistical analyses

Baseline characteristics will be summarized using descriptive statistics. The main analysis of this trial consists of a single comparison between the trial medication groups of the primary outcome after three months (dichotomized Rankin score). The analysis will be based on the intention-to-treat principle. The effect size will be expressed in a relative risk (RR) estimates and absolute risk reduction (ARR). Additionally the primary outcome will be analyzed using multivariate logistic regression, adjusting (if necessary) for clinically relevant baseline imbalances. The differences between NIHSS, ALDS scores and non-dichotomized mRS will be analyzed using the two-group *t*-test, the Mann-Whitney test, linear regression and ordinal logistic regression, when appropriate. The remaining secondary outcomes will be analyzed using simple 2 × 2 tables and logistic regression. In all analyses, statistical uncertainty will be quantified via 95% confidence intervals.

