### Randomisation

Randomisation will be performed per participating centre to ensure a equal distribution of patients between both group. The randomisation procedure will be computer- and web based, using permuted blocks. Randomisation will be stratified by centre, age (≤ 60 years, > 60 years), gender and the time between symptom onset and time of rt-PA bolus (< 2 hours, 2-3 hours, > 3 hours).

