### Data collection

At baseline following patient characteristics are collected at each participating site: age, sex, ethnicity, medical history, pre-stroke medication, pre-stroke mRS, blood pressure, Glasgow Coma Scale (GCS), National Institutes of Health Stroke Scale (NIHSS), time of symptom onset, rt-PA bolus and (if applicable) trial medication, thrombocyte count and coagulation-International Normalized Ratio. Baseline CT-scans will be collected from participating centres and assessed blindly centrally at the coordinating centre for dens media sign, early ischemic changes and degree of leukoariosis by an independent blinded neuro-radiologist.

At follow-up, neurological deficits are assessed by the NIHSS at 7-10 days or at discharge, if this is before 7 days. Clinical deterioration, defined as a 4 or more points increase on the NIHSS, will be followed by CT-scan and registration as (serious) adverse events including possible cause by each participating site. This CT-scan will be assessed at the coordinating centre as well.

Primary outcome will be assessed by a blind research nurse from the clinical trial office of the coordinating centre, who will score the mRS by telephone using a structured interview. To increase the inter-observer reliability the number of research nurses will be limited to a maximum of three. Disability will be assessed by the same research nurse during the same telephone interview using the Amsterdam Linear Disability Scale [22]. See Additional file 1 for all data collection forms.

In patients with a poor outcome at three months, the Data Collection Committee composed of the investigators of the coordinating centre and the local investigator, judges whether this poor outcome is attributed to the initial ischemic stroke, reported adverse event or other causes.

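### Covariates enter only in an additional regression triggered by observed baseline imbalance; a fixed covariate set in the primary analysis would be more precise and not depend on the data

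*Protocol article*

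**What the plan says.** Under Statistical analyses, the protocol article states: "The main analysis of this trial consists of a single comparison between the trial medication groups". The outcome is the dichotomised mRS at three months, analysed by intention to treat and reported as RR and ARR. Under Trial size, that comparison is powered on a two-group chi-square test, which has no covariates.

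Adjustment belongs to a further, additional step, in which "the primary outcome will be analyzed using multivariate logistic regression, adjusting (if necessary) for clinically relevant baseline imbalances". No covariate is named.

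Under Randomisation: "Randomisation will be stratified by centre, age (≤ 60 years, > 60 years), gender and the time between symptom onset and time of rt-PA bolus". Under Data collection, baseline NIHSS, pre-stroke mRS and age are all recorded. None of these variables is placed in the main analysis. Onset-to-bolus time returns only as a subgroup factor.

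**The concern.** Imbalance is the wrong criterion for adjustment, for two reasons.

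First, the covariate set is unknown until the baseline table has been seen. The adjusted estimate then depends on someone's view of which differences are clinically relevant. In an open-label trial it is better to close that choice in advance.

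Second, the gain in precision from a covariate comes from how well it predicts outcome, not from whether the arms differ on it. A strong predictor is worth adjusting for even when the arms match perfectly, and that is exactly when this rule leaves it out. The stratification factors are the least likely to look imbalanced, so they are also the least likely to be used.

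At stake are some power that would need no extra patients and the credibility of the adjusted result.

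**Working it through.** **Step 1: reproduce the plan's figure.** Inputs from Trial size: 0.50 v 0.40, two-sided 0.05, 400 per arm.

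- Standard error under the null: √(2 × 0.45 × 0.55 / 400) = 0.03518.
- Standard error under the alternative: √((0.25 + 0.24) / 400) = 0.0350.
- Power: Φ((0.10 − 1.96 × 0.03518) / 0.0350) = Φ(0.887) = 81.3%. With a continuity correction it is 79.3%.
- Patients per arm for 80% power: 388, or 408 with the correction.
- Confidence interval half-width: 1.96 × 0.0350 = 0.0686, against the stated 0.069.

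The plan's figures hold.

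**Step 2: power with one prespecified prognostic covariate.** The article does not say how well baseline data predict outcome, so this is a range by assumption. Outcomes were simulated from a logistic model with one normal baseline score, 400 per arm, marginal risks held at 0.50 and 0.40, and 4,000 replicates per row. The crude chi-square was compared with the Wald test of treatment in the adjusted model, on the same simulated trials.

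As a large-sample check, let R² be the variance of the individual control-arm risks divided by 0.25. Adjusted power is then about Φ(0.10 / √(0.49 × (1 − R²) / 400) − 1.96), and the required number per arm is about 388 × (1 − R²).

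| Assumed AUC | R² | Crude power | Adjusted power | Formula | Needed per arm for 80% |
|---|---|---|---|---|---|
| 0.63 | 0.056 | 0.809 | 0.829 | 0.837 | 366 |
| 0.69 | 0.112 | 0.815 | 0.852 | 0.858 | 345 |
| 0.74 | 0.174 | 0.816 | 0.876 | 0.882 | 321 |
| 0.78 | 0.235 | 0.818 | 0.903 | 0.904 | 297 |
| 0.81 | 0.293 | 0.827 | 0.930 | 0.925 | 274 |

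Worked row, AUC 0.74: 0.10 / √(0.49 × 0.826 / 400) = 3.14; 3.14 − 1.96 = 1.18; Φ(1.18) = 0.88; 388 × 0.826 = 321.

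The gain runs from 0.829 − 0.809 = 2 points to 0.930 − 0.827 = 10 points. The small drift in crude power is simulation error (standard error √(0.81 × 0.19 / 4000) = 0.006).

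**Step 3: where the gain comes from.** A second simulation (3,000 replicates) used permuted blocks of four (assumed) within centre, age, gender and time strata. It took the 37 centres named in the Discussion and assumed modest effects: log-odds 0.8 for age over 60, 0.2 per time category, a centre SD of 0.2, and none for gender.

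| Slope of NIHSS-like score | Crude | + age, gender, time | + NIHSS-like score |
|---|---|---|---|
| 0 | 0.818 | 0.821 | 0.823 |
| 1.0 | 0.822 | 0.824 | 0.898 |
| 1.5 | 0.819 | 0.821 | 0.928 |

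Age, gender and time alone add almost nothing (0.82 v 0.82). The strong covariate brings nearly all of the gain. Type I error was about 0.04 to 0.06 for every analysis in both simulations.

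**The case against.** The strongest reply is that nothing in the primary analysis is wrong. The test is prespecified, matches the sample size calculation, controls type I error and reaches its stated power. That stands. A reader might infer that the trial is underpowered or the crude test invalid, and Step 1 shows neither. The power at issue is forgone against a better analysis, not missing from the plan.

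A reader might also infer that ignoring the stratification factors costs much power. Step 3 does not support this for age, gender and time under modest assumed effects. Adjustment for centre was not tested.

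A third tempting inference is that an odds ratio from the regression conflicts with RR and ARR. It does not: the article attaches RR and ARR to the main analysis and presents the regression as additional.

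The size of the gain is assumed, and the simulations are favourable: one correctly specified prognostic score and no missing baseline data. The full recommended model, with centre, pre-stroke mRS and standardised effects, was not simulated. This also stands, so the numbers give a direction and a range, not a forecast.

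Finally, an analysis plan that is not shown might name covariates. But the article itself states both the crude main analysis and the imbalance trigger. A fixed covariate set would have to replace that rule, because it could not be read as filling it in. This part of the objection fails.

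**Conclusion.** The point holds as an improvement worth making, not as an error in the design. The crude comparison is sound and adequately powered on the plan's own assumptions. The rule that admits covariates only for observed imbalance is poor: it makes the adjusted estimate depend on choices made after seeing the data, and it discards strong predictors when the arms look balanced.

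Prespecified adjustment at the same 800 patients would raise power by about 2 to 10 points, to between 83% and 93%. This rests on an assumed baseline AUC of 0.63 to 0.81, on the planned 50% v 40%, and on baseline values being essentially complete. The direction of the gain is general; its size depends on how well NIHSS and similar variables predict outcome.

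**What to change.** Before the unblinded interim, define the primary analysis as a logistic model with treatment and a fixed covariate set:

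- baseline NIHSS, pre-stroke mRS, age, gender and onset-to-bolus time, as main effects;
- centre, either as a random effect or with small centres pooled, with the choice stated.

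Report RR and ARR by standardising the fitted risks over the trial population, with 95% confidence intervals, so that the result stays on the scale the article already uses. Keep the crude chi-square as a sensitivity analysis. Delete the imbalance trigger.

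Timing matters. The Discussion reports 361 of 800 patients included on 10 May 2010, which is 400 − 361 = 39 short of half enrolment, when the efficacy interim is due. The set is most credible if fixed and dated before that look, and in any case before final unblinding.

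The cost is small but not nil: a slightly more complex model, a simple rule for missing baseline covariates, and use of the same model at the interim. No new data are needed, because every covariate is already collected or used to stratify.

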### Outcome measures

The primary endpoint is poor functional health at 3 months defined as dependency or death (mRS 3 - 6).

The secondary objectives are:

▪ complications within 48 hours after randomisation including the occurrence of SICH and serious systemic bleeding. SICH is defined as CT-documented haemorrhage and a clinical deterioration leading to 4 or more points increase on the National Institute of Health Stroke Scale (NIHSS) as compared to the best score on the NIHSS since admission. Serious systemic bleeding is defined as a potentially life threatening bleeding which requires immediate medical intervention;

▪ neurological symptoms quantified by the NIHSS 7 - 10 days after randomisation or at discharge if the patient is discharged within 7 days;

▪ survival at 3 months;

▪ disability at 3 months assessed by the AMC Linear Disablility Scale;

▪ functional health at 3 months non-dichotomized (ordinal mRS);

▪ causes of poor outcome.

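### The plan leaves the main analysis of the day 7-10 NIHSS open and does not name baseline NIHSS as a covariate; prespecifying it would be a free gain in precision.

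*Protocol article*

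**What the plan says.** All references are to Methods and Design in the protocol article.

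- **Outcome measures** lists as a secondary outcome "neurological symptoms quantified by the NIHSS 7 - 10 days after randomisation or at discharge if the patient is discharged within 7 days".
- **Data collection** includes the same scale among the baseline items recorded at each site: "Glasgow Coma Scale (GCS), National Institutes of Health Stroke Scale (NIHSS), time of symptom onset".
- **Randomisation** names its strata: "Randomisation will be stratified by centre, age (≤ 60 years, > 60 years), gender and the time between symptom onset and time of rt-PA bolus". Baseline NIHSS is not one of them.
- **Statistical analyses** handles the NIHSS together with the ALDS and the ordinal mRS: "The differences between NIHSS, ALDS scores and non-dichotomized mRS will be analyzed using the two-group" t-test, followed by "the Mann-Whitney test, linear regression and ordinal logistic regression, when appropriate". No main method is chosen for any of the three scores, and no covariate is named.
- The same section mentions baseline adjustment once, for the primary outcome only and conditionally: "Additionally the primary outcome will be analyzed using multivariate logistic regression, adjusting (if necessary) for clinically relevant baseline imbalances".

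**The concern.** Of the three scores in that sentence, only the NIHSS has an acute-stroke baseline on the same scale among the listed items. No baseline ALDS is listed, and the baseline mRS is the pre-stroke value. All three nevertheless receive the same generic list of methods, and the NIHSS baseline is put to no stated use.

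Two of the four methods, the t-test and the Mann-Whitney test, cannot take a covariate. The two regressions can, but a linear regression on arm alone gives the same comparison as the t-test. As written, an analyst could report an unadjusted comparison and be fully in line with the article.

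The stake is efficiency and ease of reading. If day 7-10 NIHSS correlates with baseline NIHSS, leaving baseline out gives a wider interval than necessary. If the arms happen to differ in severity, readers will have to guess how much of the observed difference reflects that.

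**Working it through.** **1. The plan's own figures (section Trial size).** Inputs: 0.50 versus 0.40, two-sided 0.05, 80% power, 400 per group.

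- Chi-square without continuity correction: n = [1.96·√(2·0.45·0.55) + 0.8416·√(0.25 + 0.24)]² / 0.10² gives 388 per group. With continuity correction it is 408. The stated 400 lies between them, and power at 400 is 81.3%.
- Half-width of the 95% interval: 1.96·√(0.49/400) = 0.0686 (stated 0.069).
- Odds ratio: (0.4/0.6)/(0.5/0.5) = 0.667 (as stated).
- Standardised difference of 0.20, given for the ALDS: power 80.7% at 400 per group.

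All of these reproduce. No figure is stated for the NIHSS.

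**2. Unadjusted comparison of day 7-10 NIHSS.** Assume 400 scored patients per arm.

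- Standard error of the difference in SD units: √(2/400) = 0.0707.
- Difference detectable with 80% power: (1.96 + 0.8416)·0.0707 = 0.198 SD.

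**3. Linear ANCOVA on baseline NIHSS.** Let r be the correlation between baseline and day 7-10 NIHSS. The documents give no value, so a range is shown. Adjustment multiplies the variance of the difference by (1 − r²) and the standard error by √(1 − r²). The total that matches the unadjusted precision of 800 patients is 800·(1 − r²). Power at an illustrative 0.20 SD is Φ(0.20/(0.0707·√(1 − r²)) − 1.96). The 0.20 is borrowed from the ALDS benchmark.

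| r (assumed) | Variance reduction | SE ratio | Equivalent total | Detectable difference (SD) | Power at 0.20 SD |
|---|---|---|---|---|---|
| unadjusted | 0% | 1.000 | 800 | 0.198 | 80.7% |
| 0.3 | 9% | 0.954 | 728 | 0.189 | 84.3% |
| 0.5 | 25% | 0.866 | 600 | 0.172 | 90.4% |
| 0.7 | 49% | 0.714 | 408 | 0.141 | 97.7% |
| 0.8 | 64% | 0.600 | 288 | 0.119 | 99.7% |

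**4. Chance differences in severity.** With 400 per arm, the difference in mean baseline NIHSS has a 95% range of ±1.96·0.0707 = ±0.139 SD. A difference at that limit would move an unadjusted day 7-10 comparison by r·0.139, that is 0.04 SD (r = 0.3) to 0.11 SD (r = 0.8). The unadjusted standard error already allows for this.

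**5. Scope.** The (1 − r²) factor belongs to linear ANCOVA. In an ordinal logistic model, adding baseline NIHSS changes the odds ratio to one conditional on baseline severity, and its standard error does not shrink by that factor. The table cannot be applied to that option.

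**The case against.** The strongest objection is that no unadjusted analysis is prescribed. Two of the four methods can carry a baseline term, and because linear regression without covariates repeats the t-test, listing it separately can be read as leaving room for adjustment. This stands. A reader who stops at the t-test might infer that the article commits to a raw two-group comparison; the rest of the sentence does not support that.

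A second objection is that covariates for a secondary outcome are commonly left to the full protocol or the SAP, neither of which is shown. This stands in part, and it keeps the point low in priority. It does not dispose of the point: the section does address adjustment, confines it to the primary outcome, and then lists four methods for the NIHSS without ranking them. The recommendation is also a specific, better use of data already collected, and not merely a request for detail.

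Third, a reader might infer that a chance imbalance in severity would bias the comparison. It would not. Randomisation balances severity in expectation, the unadjusted test keeps its type I error, and its interval already includes chance imbalance. What remains is lost precision and a single result that is harder to interpret.

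Fourth, the size of the gain rests on an assumed correlation. That is correct. At 0.3 the gain is modest, and at the 0.20 SD benchmark the unadjusted comparison already has about 80.7% power.

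**Conclusion.** The point holds in a limited form. For the day 7-10 NIHSS the article permits an unadjusted comparison, names no main analysis and makes no stated use of a baseline score that is collected and not balanced by stratification. Such a comparison is valid but may be less precise than it need be.

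Under linear ANCOVA with 400 scored patients per arm, the avoidable variance is 9% to 64% for an assumed correlation of 0.3 to 0.8, and 25% to 49% for 0.5 to 0.7. Both the correlation and complete scoring are assumptions.

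One secondary outcome is affected. The primary mRS analysis and the total of 800 do not change. This is a low-priority free improvement and not an error in the plan.

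**What to change.** Add one sentence to Statistical analyses, or confirm it in the SAP: the main analysis of the day 7-10 NIHSS is a regression on treatment arm with baseline NIHSS as a prespecified covariate, included whether or not an imbalance is seen. Use linear ANCOVA, or the ordinal logistic model already listed if the scores are too skewed, and state in advance how that choice will be made. Keep the t-test or Mann-Whitney result as a supporting analysis.

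The cost is one sentence, with no new data and no extra patients. Two small matters go with it. Any patient without a baseline NIHSS needs a stated rule for that covariate. If the ordinal model is used, its odds ratio should be reported as conditional on baseline severity.

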### Interim analysis

Besides interim analyses on the safety data the DSMB will also perform an unblinded interim analysis on the primary outcome to assess the strength of the efficacy data when half of the patients are enrolled. The DSMB will also check the assumptions for sample size calculations. The analysis will be performed by an independent statistician of the Academic Medical Centre Clinical Research Unit, who is not involved in managing the trial. The DSMB can recommend the Steering Committee of the ARTIS-Trial to

▪ adjust the sample size;

▪ early terminate the study when there is clear and substantial evidence of benefit;

▪ early terminate the study in case the data suggests no benefit or in case accrual rates are too low to provide adequate statistical power for identifying the primary endpoint.

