Several cohort studies could not find a significant association between pre-treatment with antiplatelet agents and SICH [27-30]. Other prospective observational studies observed even a net benefit in favourable outcome after 3 months in patients using antiplatelet drugs prior to rt-PA thrombolysis, despite a strong relationship between this antiplatelet therapy and SICH [18,19]. Recent results from the large SITS-MOST registry of more than 6,000 stroke patients treated with intravenous rt-PA confirmed the increased risk of SICH in patients with antiplatelet pre-treatment [31]. Previous use of aspirin had an odds ratio of 1.58 (95% CI 1.04 - 2.39) of SICH per SITS-MOST definition, a remote parenchymal haemorrhage type 2 on the 22 - 36 hours follow-up imaging scans after the start of thrombolysis treatment. The clinical relevance of these SICH remains to be determined since independency and mortality within 3 months were not associated with previous aspirin use in this registry. Although prior antiplatelet therapy is a contra-indication in this protocol, we are aware of the possible increased risk of SICH due to the combination of rt-PA and aspirin. Therefore, the DSMB will continuously monitor serious adverse events in relation to efficacy outcome measures.

ARTIS is a randomised controlled trial investigating the efficacy of the acute addition of aspirin to intravenous rt-PA thrombolysis in patients with acute ischemic stroke. ARTIS will answer a highly relevant question in acute stroke care by means of a simple adjustment of current antiplatelet regimen with regard to rt-PA thrombolysis. A condensed version of the protocol has been published in Cerebrovascular Diseases [32].

The ARTIS-Trial has started at the end of 2008. Thirty-seven centres are actively randomizing patients. As of May 10^th ^2010, 361 of the 800 patients have been included so far. This trial is set up in the Netherlands. However, other centres - also from foreign countries - experienced in thrombolysis are invited to participate as well. The principle investigator can be contacted by e-mail.

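### The interim look allows a stop for benefit with no numerical boundary while the final test keeps an unreduced 0.05, so the 5% two-sided error rate is not guaranteed

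*Protocol article*

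**What the plan says.** The Interim analysis section of the protocol article provides for one unblinded analysis of the primary outcome when half the patients are enrolled, done by an independent statistician for the DSMB. The DSMB may then recommend that the Steering Committee "early terminate the study when there is clear and substantial evidence of benefit". It may also recommend stopping because no benefit is suggested or accrual is too slow, or changing the sample size. That wording is the only criterion for a benefit stop.

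The Trial size section describes a fixed design: a chi-square test "with a 0,05 two-sided significance level will have 80% power to detect the difference" between 50% and 40% poor outcome, with 400 patients per group. It adds that "a two-sided 95% confidence interval for the difference between the proportions will extend 0,069" from the observed difference. The Statistical analyses section calls the main analysis one comparison of the dichotomised Rankin score and uses 95% intervals in every analysis. Neither section mentions the interim look or a reduced final level.

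Two further places describe the DSMB's work. Under Safety reporting it is to "focus on both safety monitoring and analysis of effectiveness on unblinded data". In the Discussion, "the DSMB will continuously monitor serious adverse events in relation to efficacy outcome measures".

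**The concern.** A trial that may stop for benefit on its primary endpoint has two chances to claim success. If the final test still uses the whole 0.05, the overall error exceeds 5% by an amount that depends on the interim threshold. The article states a level, one comparison and a confidence level as if the first chance did not exist, and leaves the threshold to judgement on unblinded data.

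The contingency is not remote. Under the design assumptions the expected interim Z with 200 per arm is 0.10/√(0.49/200) = 2.02. A DSMB that took p<0.05 as sufficient would then stop about half the time. At stake are the error rate attached to a positive result and, after an early stop on a lenient threshold, an overstated effect.

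**Working it through.** **Inputs from the article.** Two-sided alpha 0.05, power 80%, poor outcome 0.50 versus 0.40, 400 per group (Trial size); one look at half enrolment (Interim analysis). **Assumptions.** Equal allocation, no dropout, sample size not changed at the look, and information fraction t = 0.5 (0.40 as a sensitivity case, because the 3-month outcome lags enrolment).

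**1. The article's own figures.**
- Sample size: n = [1.96·√(2·0.45·0.55) + 0.8416·√(0.25 + 0.24)]²/0.10² = (1.379 + 0.589)²/0.01, which gives 388 per group (408 with continuity correction). The stated 400 is consistent, with power 81.3%.
- Odds ratio: (0.40/0.60)/(0.50/0.50) = 0.667.
- Interval half-width: 1.96·√((0.25 + 0.24)/400) = 1.96 × 0.035 = 0.0686, stated as 0.069.

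All reproduce as a fixed design with no allowance for an interim look.

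**2. Overall error with the final test at 0.05.** Under the null, the interim and final statistics Z1 and Z2 are bivariate normal with correlation √t = 0.707. Overall two-sided error = 1 − P(|Z1| < c1 and |Z2| < 1.96).

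| Interim threshold | c1 | Error, t = 0.5 | Error, t = 0.40 |
|---|---|---|---|
| p<0.05 | 1.960 | 8.3% | 8.6% |
| p<0.01 | 2.576 | 5.46% | 5.57% |
| p<0.005 | 2.807 | 5.19% | 5.25% |
| p<0.001 | 3.291 | 5.02% | 5.04% |

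Simulating 1,000,000 two-arm binomial trials (200 then 400 per arm, true rate 0.45 in both) with a p<0.05 look also gives 8.3%.

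**3. Counting only early stops for benefit.** Error = 1 − P(Z1 < c1 and |Z2| < 1.96): 6.7%, 5.23%, 5.09% and 5.01% for the same four thresholds at t = 0.5.

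**4. False claims of benefit (nominal 2.5%), without and with futility stopping.** Without it, the rate is 4.16% with a p<0.05 look and 2.51% with p<0.001. If the trial also stopped whenever the interim Z was below 0, these become 4.13% and 2.48%.

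**5. Boundaries that hold 5% overall at t = 0.5.**

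| Boundary | Interim p | Final p | Power, 400 per arm | n per arm for 80% |
|---|---|---|---|---|
| O'Brien-Fleming | 0.0052 | 0.0480 | 81.2% | 392 |
| Lan-DeMets, O'Brien-Fleming type | 0.0031 | 0.0490 | 81.4% | 390 |
| Haybittle-Peto | 0.001 | 0.0498 | 81.5% | 389 |
| Pocock | 0.0294 | 0.0294 | 77.3% | 431 |

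The power column uses the unpooled variance, under which the fixed design has 81.5%. Only a Pocock-type boundary would need more than the planned 400.

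**The case against.** The strongest reply is that a journal article condenses the full protocol, and that a numerical boundary commonly sits in the analysis plan or a DSMB charter, neither of which is shown. Its absence alone is weak evidence, and that part stands. What remains is in the article itself: it prints a stopping criterion for the primary endpoint, and it also prints an unreduced level and one comparison that take no account of that criterion.

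The second reply is that the verbal criterion suggests something much stricter than p<0.05. That is fair. At p<0.001 the excess is 0.02 percentage points, and stopping for no benefit can bring the false-benefit rate just under 2.5%. The 8.3% is an upper illustration that counts stops in either direction. Futility stopping does little for the lenient case, however, where the false-benefit rate stays near 4.1%.

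A reader might also infer from Safety reporting and the Discussion that efficacy is tested repeatedly, so that the number of looks is inconsistent. The documents do not support this. Safety reporting gives a general remit, which the one planned look satisfies, and its termination power there concerns harm. The Discussion describes serious adverse events weighed in the context of efficacy. Neither adds a formal efficacy test or a benefit stop, so error rates for several looks would model a design the article does not plan.

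Finally, the DSMB only recommends, and the analysis is done by an independent statistician. Both are good safeguards, but neither fixes the threshold.

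**Conclusion.** The point holds as a should-fix. The stated two-sided 5% is not guaranteed: with one look at half the information and the final test at 0.05, it lies between 5.02% (interim p<0.001) and 8.3% (interim p<0.05), before any reduction from futility stopping. At an information fraction of 0.40 the range is 5.04% to 8.6%.

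A reader might go further and conclude that the 5% level is not delivered. That does not follow, because the size of the excess rests on a threshold the article does not give, and a strict one makes it negligible. The planned 400 per group is not in error. The result rests on the assumptions listed with the inputs and on no reduced final level being set in a document not shown.

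**What to change.** In the Interim analysis section, before the half-enrolment look, state a conservative benefit boundary and its matching final level. Acceptable examples are Haybittle-Peto (interim p<0.001, final 0.0498; a rounded 0.049 is slightly conservative, overall 4.92%) or an O'Brien-Fleming type boundary with a final level of about 0.048 to 0.049. Carry the final level into the Trial size and Statistical analyses sections. Add one sentence saying that this is the only comparative efficacy test with a benefit stop, and that the DSMB review described under Safety reporting and in the Discussion carries none.

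Timing matters. The Discussion reports 361 of 800 patients included by May 2010, and half enrolment is 400. A rule fixed before the unblinded look is credible in a way that one chosen afterwards is not.

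The cost is wording only. Power stays at about 81% with 400 per arm and no patients are added. The downside is that stopping early for benefit becomes harder.
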